# Improved self-management skills in Chinese diabetes patients through a comprehensive health literacy strategy: study protocol of a cluster randomized controlled trial

**DOI:** 10.1186/1745-6215-15-498

**Published:** 2014-12-20

**Keywords:** Cost-effectiveness, Cost-utility, Diabetes self-management, Hemoglobin A1c, Literacy, Numeracy, Self-efficacy, Self-management behaviors

## Abstract

**Background:**

Diabetes self-management often involves the interpretation and application of oral, written, or quantitative information. Numerous diabetes patients in China have limited health literacy, which likely leads to poorer clinical outcomes. This study is designed to examine the efficacy and cost-effectiveness of addressing health literacy to improve self-management skills and glycemic control in Chinese diabetes patients.

**Methods/design:**

This is a cluster randomized controlled trial (RCT) conducted in 20 community healthcare sites in Shanghai, China. Overall, 800 diabetes patients will be randomized into intervention and control arms and will have a baseline hemoglobin A1c (HbA1c) assay and undergo a baseline survey which includes measures of health literacy and diabetes numeracy using revised Chinese versions of the Health Literacy Management Scale and Diabetes Numeracy Test Scale. During the 1-year period of intervention, while the control group will receive usual care, the intervention group will be supplemented with a comprehensive health literacy strategy which includes i) training healthcare providers in effective health communication skills that address issues related to low literacy, and ii) use of an interactive Diabetes Education Toolkit to improve patient understanding and behaviors. Assessments will be conducted at both patient and healthcare provider levels, and will take place upon admission and after 3, 6, 12, and 24 months of intervention. The primary outcome will be the improvement in HbA1c between Intervention group and Control group patients. Secondary outcomes at the patient level will include improvement in i) clinical outcomes (blood pressure, fasting lipids, body mass index, weight, smoking status), ii) patient reported self-management behaviors, and iii) patient-reported self-efficacy. Outcomes at the provider level will include: i) provider satisfaction and ii) intensity and type of care provided. The effects of the intervention will be examined in multivariable general linear models. Both cost-effectiveness and cost-utility analyses will be performed.

**Discussion:**

The main strengths of this study are its large sample size and RCT design, involvement of both patients and healthcare providers, and the long term follow-up (24-months). This project will help to demonstrate the value of addressing health literacy and health communication to improve self-management and clinical outcomes among Chinese diabetes patients.

**Trial registration:**

ISRCTN76130594, Registration date: Sept 22, 2014.

**Electronic supplementary material:**

The online version of this article (doi:10.1186/1745-6215-15-498) contains supplementary material, which is available to authorized users.

## Background

The rising worldwide prevalence of type 2 diabetes mellitus (T2DM) has been very well documented. In China, the prevalence of T2DM tripled between 1980 (about 1.0%) and 1996 (3.2%) [1, 2], and reached 9.7% in 2008 among adults at 20 years old or above [3]. It is estimated that over 92 million adults in China have T2DM; this represents approximately half of the world’s diabetic population and places China at the “*global epicenter of the diabetes epidemic*” [4].

T2DM is a chronic condition that requires patients to follow specific recommendations and prescriptions for the rest of their lives. Due to the lifelong health care it entails and the huge number of diabetic patients, diabetes self-management has become a major component of comprehensive diabetes care around the world. However, less than 50% of recommended guidelines for diabetes management are currently achieved in the United States [5, 6]. In China, where the diabetes self-management strategy has been applied for a couple of years and diabetes education has been suggested to achieve better glycemic control [7, 8], only one-fifth of diabetic patients were reported to achieve hemoglobin A1c (HbA1c) levels of less than 6.5% [9]. One possible reason for this modest effect may be that previous diabetes management did not specifically address issues of health literacy or numeracy. The self-management of diabetes often involves interpretation of quantitative information and the performance of calculations. However, a large number of patients have poor health literacy and numeracy, which lead to incomprehension of basic health information, lower likelihood of receiving preventive care, limited ability to take medications appropriately, higher hospitability, poorer glycemic control status, and worse clinical outcomes.

Literacy has been defined as “*an individual*’*s ability to read*, *write*, *speak*, *and compute and solve problems at levels of proficiency necessary to function on the job and in society*, *to achieve one*’*s goals*, *and develop one*’*s knowledge and potential*” [10]. Patients with low literacy may have trouble in reading prescriptions, following medical instructions, and interacting with the health care system. Patients with low literacy usually have lower disease-specific knowledge, report lower quality of life, and have poorer health related outcomes – even after adjusting for potential confounders such as educational level, insurance, and other factors [10–12]. Numeracy, as an important component of literacy, can be defined as the ability to understand and use numbers in daily life [13]. Numeracy is particularly important to patients with diabetes because diabetes requires self-management skills that rely on mathematics such as counting carbohydrates, interpreting glucose monitoring, applying a sliding scale for insulin, and calculating insulin doses based on carbohydrate intake. These skills require not only basic math skills, but also the ability to apply those math skills in the context of diabetes care (that is, diabetes-related numeracy).

Low literacy is common among patients with diabetes, and appears closely associated with less knowledge of diabetes self-management and worse clinical outcomes [11, 12, 14, 15]. Williams et al. [15] found that 55% of diabetes patients in the United States had inadequate literacy. It was reported that, of patients with inadequate literacy, 50% did not know the symptoms of hypoglycemia, 62% did not know how to treat hypoglycemia, and 42% did not know the normal blood glucose range despite the fact that 73% of the patients had attended previous diabetes education. Among over 400 patients with diabetes, Schillinger et al. [14] observed an independent association of poor literacy with worse glycemic control and higher rates of retinopathy. Most of the studies, to date, on the role of literacy in health care have focused specifically on verbal literacy with little examination of quantitative skills. While there is a strong correlation between verbal literacy and quantitative skills, there are many patients who have adequate verbal literacy but are still unable to use math skills appropriately or are anxious/intimidated about math [16].

Recent studies have demonstrated that providing low literacy materials or low literacy forms of communication can improve patient comprehension for patients with both low and high literacy [17, 18]. A randomized controlled trial (RCT) of a comprehensive disease management intervention demonstrated that literacy was a significant factor in predicting patients’ improvement in HbA1c from the intervention, and suggested that addressing literacy could improve patient outcomes [11]. Two coordinated RCTs performed at two academic medical centers of the United States from 2006 to 2008 rigorously examined the role of addressing both literacy and numeracy, and found that the literacy- and numeracy-sensitive diabetes care can lead to significant improvements in glycemic control, self-efficacy, and other outcomes [19].

So far, very few studies have been specifically designed to address the association of literacy and numeracy with diabetes self-management skills in China. A survey conducted in older diabetes patients in Beijing showed that diabetes knowledge was very limited in this population [20]. In a study conducted in Hong Kong, a negative correlation was observed for health literacy with diabetic control status among diabetes patients [21]. Innovative approaches to diabetes management and education are urgently needed in this population, who has a high prevalence of diabetic complications. Addressing literacy and numeracy through improved healthcare provider communication skills and improved educational materials is a potentially successful strategy. It is an innovative approach to optimize patient understanding, promote shared decision-making, and enhance patient self-efficacy and self-management behaviors. In the current study, we will develop a comprehensive health literacy strategy and evaluate its utility among Chinese diabetes patients. We will report the outcomes of the economic evaluation in a separate article.

The primary outcome of the current study is improvement in HbA1c. We hypothesize that participants randomized to the intervention arm will have a significantly lower HbA1c level when compared to the control group participants. Secondary outcomes are improvements in blood pressure, lipids, self-management behavior, self-efficacy, and other patient outcomes important to improving diabetes care, as well as improved health communication skills and increased satisfaction in health care providers. We hypothesize that patients in the intervention condition will report beneficial changes while the health care providers will be more satisfied with treatment than those in the control condition. A further aim of this study is to evaluate the cost-effectiveness and cost-utility of the intervention. We hypothesize that the intervention will be performed on a large scale in a way that is practical, cost-effective, and sustainable.

## Methods

### Study design

This is a cluster RCT with blinded data analysis (Figure 1). Prior to the trial, we conducted a validation study in 408 diabetes patients in Pudong New area of Shanghai to assess the validity of diabetes-related numeracy test scale in Chinese patients (C-DNT-5). We also performed a pilot study in 80 diabetes patients from eight Community Healthcare Centers in Minhang and Changning district of Shanghai, China, to examine the feasibility and acceptability of intervention and research procedures. We obtained informed consent from each study participant. The results of the two studies have been used to inform the development of the forthcoming trial.

**Figure 1 Fig1:**
[figure not shown]
**Flowchart of the study.**

### Setting

A total of 800 diabetes patients will be recruited from eight Community Healthcare Centers in Minhang and Changning district of Shanghai, China. Five clinic sites will be selected from each Center. All clinic sites meet the following criteria: i) at least 20 patients can be recruited per site; ii) at least 2 to 4 physician(s), nurse practitioner(s), or diabetes educator(s) per Center can participate in the intervention; iii) the site agrees to participate for a minimum of 2 years; and iv) the site agrees to be randomized to either arm of the study.

### Inclusion and exclusion criteria for participants

Inclusion criteria at the patient level will include: i) patient has a clinical diagnosis of T2DM; ii) age 18 to 85 years; iii) most recent HbA1c ≥7.5%; iv) patient provides signed informed consent form; and v) patient agrees to participate in the study for the full 2-year duration. Exclusion criteria at the patient level will include: i) poor visual acuity (vision worse than 20/50 using Rosenbaum Pocket Screener); ii) significant dementia or psychosis (by health provider report or chart review); and iii) terminal illness with anticipated life expectancy <2 years.

### Analytical power

According to our previous survey, the mean (SD) of HbA1c among 934 randomly selected diabetes patients was 8.0% (1.4%) [22]. We anticipate a 0.8% improvement in HbA1c level from baseline to 12 months, with a conservative estimate of the SD at 2.0. We performed a simulation study generating follow-up HbA1c using the following formula: Follow-up HbA1c = Baseline HbA1c + β* Group + Site Effect + Provider Effect + δ. Group is a binary variable indicating 0 for control and 1 for intervention group. For 800 patients recruited, we anticipate n = 560 for the final analysis after subtracting 30% loss to follow-up. We will perform multiple imputation for the missing data where all 800 subjects will be used in the analysis; however, our sample size is estimated with the analysis excluding missing observations to provide the most conservative estimate. Assuming 0.8% reduction in HbA1c with the intervention compared with the control group at 12-month follow-up, the proposed analysis will yield analytical power of 100.0% with two-sided 5% significance level.

A simpler sample size calculation than our simulation model would not account for the double clustering design. Using a popularly used formula estimating sample size with single clustering for 40 sites, power is also 100.0% with two-sided 5% significance level to detect the difference of 0.8% in HbA1c.

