### Randomization procedure

Randomization will occur at the level of the Community Healthcare Centers. Four Centers (20 clinic sites) will be randomized to receive the intervention and four centers (20 clinic sites) will be randomized to the control condition. To minimize potential imbalance in randomization, we will employ a multivariable score based pair-wise matching method [23] to achieve the optimal balance by location, size, population covered, HbA1c level, and other characteristics of recruited patients including age, gender, insurance status, insulin status, and body weight. We will first weigh covariates according to relevance of potential bias introduced, and then compute a multivariable score using an established algorithm after data are standardized and appropriately weighted. We will then identify four matched pairs, with each pair consisting of two facilities with closest multivariable scores. Randomization will be performed within each pair, with one Center randomized to receive the intervention, and the other to the control condition. This process will be repeated to obtain all possible pair-wise combinations for randomization. We will then assess balance for each covariate as a proportion of imbalance detected over all combinations. When balance is not ideal, the process will be repeated after adjusting the weighting system. After an appropriate weighting scheme is determined, the centers will be paired and a final randomization will be performed. This procedure will ensure more comparable patient populations with respect to clinic characteristics. Randomization at the Center level will help avoid contamination issues at the healthcare provider level.

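### The stated 100.0% power omits the randomised unit: it is built on site and provider effects and on 40 sites, while only 8 Centers are randomised

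*Protocol article*

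**What the plan says.** All references are to the protocol article.

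- **Setting:** eight Community Healthcare Centers take part, with five clinic sites from each, so 8 × 5 = 40 sites.
- **Randomization procedure:** "Randomization will occur at the level of the Community Healthcare Centers". Four Centers go to each arm, by randomisation within four matched pairs.
- **Analytical power, simulation:** follow-up HbA1c is generated from baseline plus "Group + Site Effect + Provider Effect" plus a residual. For a 0.8 difference between arms at 12 months and 560 analysed patients, it is said that "the proposed analysis will yield analytical power of 100.0"%, two-sided 5%.
- **Analytical power, cross-check:** a common formula is used, "estimating sample size with single clustering for 40 sites, power is also 100.0"%.

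No Center term, count of Centers, pairing, ICC or variance component appears in the power section.

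**The concern.** Group is constant within a Center, so variation between Centers adds directly to the error of the treatment comparison, and only 8 allocated units are available to average it out. Effects that are independent between sites do not represent this, because the five sites of a Center never split between arms. A calculation that stops at the site understates the variance of the comparison and overstates its degrees of freedom.

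The article itself suggests that Centers may differ. HbA1c is measured on each Center's own equipment (Collection of measures), Centers are matched on HbA1c and patient mix (Randomization procedure), and usual care differs between the two districts (Discussion).

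At stake is how a non-significant result would be read. Power of 100.0% says that such a result all but rules out a 0.8 effect. If power is materially lower, that reading is wrong.

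**Working it through.** **Inputs from Analytical power:** difference 0.8; planning SD 2.0 (survey SD 1.4 as a sensitivity value); 560 analysed, 280 per arm; two-sided 5%. **From Setting and Randomization procedure:** 40 sites, so 560/40 = 14 analysed patients per site; 8 Centers, so 560/8 = 70 per Center; 4 against 4, in 4 pairs. **Assumed:** the ICC, shown over 0 to 0.05 because the article gives none.

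**Formulas:** SE = SD × √[(4/560) × (1 + (m − 1) × ICC)], with m patients per cluster. Power is the probability that a noncentral t with noncentrality 0.8/SE exceeds the 97.5% point of t. That point is 2.024 for 38 df (40 sites), 2.447 for 6 df (8 Centers, unpaired) and 3.182 for 3 df (four pairs).

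**Step 1: the plan's own figure.** Without clustering, SE = 2.0 × √(4/560) = 0.169, 0.8/0.169 = 4.73, and the normal approximation gives 99.7%. With 40 sites it gives 99.4%, 98.8% and 95.8% at site ICC 0.01, 0.02 and 0.05 (99.1%, 98.4% and 94.8% with 38 df). So the stated figure is roughly recovered if the site ICC is small, although a literal 100.0% is not reached at SD 2.0 with 560 patients even at ICC 0. With SD 1.4 the 40-site formula does round to 100.0% at ICC 0.01 and 0.02.

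**Step 2: the randomised unit.** With m = 70 the design effect is 1 + 69 × ICC, that is 1.69, 2.38 and 4.45 at ICC 0.01, 0.02 and 0.05.

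| Center ICC | SE (SD 2.0) | SD 2.0, 6 df | SD 2.0, 3 df | SD 1.4, 6 df | SD 1.4, 3 df |
|---|---|---|---|---|---|
| 0 | 0.169 | 97.4% | 86.9% | 99.98% | 98.8% |
| 0.01 | 0.220 | 85.6% | 68.3% | 99.0% | 91.8% |
| 0.02 | 0.261 | 72.5% | 55.0% | 95.1% | 82.0% |
| 0.05 | 0.357 | 47.0% | 34.5% | 76.1% | 58.3% |

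The 3 df columns assume that matching removes no between-Center variance. If it removes half (design effect 1 + 69 × ICC − 35 × ICC), the 3 df figures at ICC 0.01, 0.02 and 0.05 become 77%, 69% and 50% with SD 2.0, and 96%, 92% and 78% with SD 1.4.

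**Step 3: thresholds.** At SD 2.0, power falls below 80% once the Center ICC exceeds about 0.014 (6 df) or 0.003 (3 df, no matching gain). The difference detectable with 80% power is about 3.37 × SE at 6 df: 0.57, 0.74, 0.88 and 1.20 at ICC 0, 0.01, 0.02 and 0.05. At 3 df it is about 4.25 × SE: 0.72, 0.93, 1.11 and 1.52.

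**Step 4: simulation check** (20,000 runs, SD 2.0, Center ICC 0.02 and site ICC 0.02). A Center-level t-test has 68% power unpaired and 51% paired, and holds its 5% level. A test that treats the 40 sites as independent shows 92% apparent power but rejects a true null 14.7% of the time.

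**The case against.** The strongest reply is that the size of the loss rests on an ICC from outside the article. That stands. If Center variance were zero, a 40-site analysis would be valid, with about 98% power at site ICC 0.02. The article calls SD 2.0 conservative. With SD 1.4 and 6 df, power is still 95% at ICC 0.02. Adjustment for baseline HbA1c (Statistical analyses) and matching on HbA1c, location and district should reduce both residual and between-Center variance, and the tabulated figures take no credit for this. The lowest values need SD 2.0 together with either ICC 0.05, or 3 df without matching gain at ICC 0.02 or more. A reader might infer that a null result is quite likely even if the effect is real; that holds for only part of the range.

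Second, a reader might infer that the simulation amounts to 40 independently randomised sites. That is shown only for the cross-check formula. Setting asks for at least 2 to 4 providers per Center, so at those minimum counts 16 to 32 providers serve 40 sites. A provider could then span several sites of one Center, and the provider term could carry some within-Center correlation. The nesting and variances are not given. Usage of the word site is also loose: one site criterion in Setting speaks of the site being randomised. Reading Site Effect as clinic site is an inference, but the 40-site cross-check makes it much the likelier one.

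Third, the 6 and 3 df figures presume a Center-level test, which Statistical analyses does not name. They show what the allocated units can support; they do not describe the planned model.

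None of this restores the 100.0%. A zero Center variance is neither stated nor justified, and at the planning SD a Center-level test does not reach 100.0% even at ICC 0.

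**Conclusion.** The point holds in a limited form. The cross-check uses the wrong number of clusters for this allocation, and the simulation as written has no term at the randomised level, so neither supports 100.0% power. This is a fault in the specification of the power model, not a slip of arithmetic. At the planning SD, Center-level power runs from 97% down to 47% (6 df) or from 87% down to 35% (3 df, no matching gain) over an assumed Center ICC of 0 to 0.05. At SD 1.4 it runs from about 100% to 76%, or from 99% to 58%. Effective matching or baseline adjustment would raise these figures.

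The article does not support the stronger conclusion that the trial is underpowered: how likely a false null result is depends on a Center ICC and an SD that have yet to be stated. Nor does the point turn on the abstract's remark that "The main strengths of this study are its large sample size and RCT design". Sample size is one of several strengths listed there, and rewording it would be an editorial choice.

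**What to change.** In Analytical power, add a Center effect and the matched pairs to the existing simulation, and state the variance components or ICCs assumed for Center, site and provider and how providers are nested. Base the cross-check on 8 Centers, four per arm, with small-sample degrees of freedom (6, or 3 if the pairs are analysed). Replace both 100.0% statements with power over a stated range of Center ICC and SD, for example ICC 0 to 0.05 and SD 1.4 to 2.0, together with the corresponding detectable difference. Any credit for matching or baseline adjustment should be entered as an explicit assumption.

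The cost is a re-run of a simulation that already exists and a few changed sentences, with a less favourable power figure as the result. Correcting the statement requires no change to enrolment or allocation, so it can be made while recruitment is ongoing.

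### The stated 100.0% power counts 40 clinic sites as clusters, but eight Centers are randomized; with the Center level left out, the design does not support that figure

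*Protocol article*

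**What the plan says.** **Power.** The Analytical power section models follow-up HbA1c as baseline plus a group effect, a site effect, a provider effect and a residual. "Assuming 0.8% reduction in HbA1c with the intervention compared with the control group at 12-month follow-up", and with 560 of 800 patients analysed after 30% loss, it concludes that "the proposed analysis will yield analytical power of 100.0% with two-sided 5% significance level". A simpler check follows: "Using a popularly used formula estimating sample size with single clustering for 40 sites, power is also 100.0% with two-sided 5% significance level". The planning SD is introduced "with a conservative estimate of the SD at 2.0"; the same section reports an SD of 1.4 from an earlier survey of 934 patients. No ICC or variance component is given.

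**Allocation.** The Randomization procedure section says: "Randomization will occur at the level of the Community Healthcare Centers". Eight Centers form four matched pairs and one Center of each pair goes to each arm, giving four Centers and 20 sites per arm. The Setting section selects five sites in each Center, so there are 40 sites.

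**Abstract.** The abstract describes a "cluster randomized controlled trial (RCT) conducted in 20 community healthcare sites in Shanghai, China".

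**The concern.** In a cluster trial, the evidence about treatment is limited by the number of randomized units and by how much they differ from one another. The five sites of a Center always share one allocation. Any difference between Centers therefore moves all five sites, and about 70 analysed patients, in the same direction. Counting sites as the clusters removes that component from the standard error of the treatment effect.

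The article itself gives reasons to expect Center differences. It matches Centers on location, size, population covered and HbA1c. It measures HbA1c on equipment held in each Center. Its Discussion says usual care differs somewhat between the two districts.

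At stake is how the trial will be read. A plan that claims certainty of detecting 0.8% invites a null result to be taken as evidence of no effect, when the design may have had only moderate power.

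**Working it through.** **Inputs from the article:** difference 0.8; two-sided 5%; 560 analysed (280 per arm); SD 2.0 (planning) and 1.4 (survey); eight Centers, four per arm; 40 sites. Hence 560/40 = 14 analysed patients per site and 560/8 = 70 per Center.

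**Assumed:** the ICC, at 0.01, 0.02 and 0.05, because none is stated.

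**Formulas.** Design effect DE = 1 + (m − 1) × ICC, with m patients per cluster. SE = SD × √[(4/560) × DE]. Power comes from the normal distribution for the 40-site check, and from the noncentral t with noncentrality 0.8/SE when the Center is the unit.

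**Step 1: the article's own figure, 40 sites, m = 14.** DE = 1 + 13 × ICC = 1.13, 1.26 and 1.65.
- SD 2.0: power 99.4%, 98.8% and 95.8%.
- SD 1.4: 99.95% or more up to an ICC of about 0.05, which prints as 100.0%.

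The stated figure is therefore reproduced at SD 1.4, and to within 2 points at SD 2.0 if the site ICC is about 0.03 or less. The calculation works for 40 independent clusters. The question is whether it describes this design.

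**Step 2: the Center as unit, m = 70.** DE = 1 + 69 × ICC = 1.69, 2.38 and 4.45. For example, at SD 2.0 and ICC 0.01, SE = 2.0 × √(0.007143 × 1.69) = 0.220 and 0.8/0.220 = 3.64. Comparing four Center means with four leaves 8 − 2 = 6 df. A matched-pair test on four pairs leaves 3 df; the paired columns give no credit for variance removed by matching.

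| Center ICC | DE | SE, SD 2.0 | Power, 6 df | Power, paired 3 df | SE, SD 1.4 | Power, 6 df | Power, paired 3 df |
|---|---|---|---|---|---|---|---|
| 0.01 | 1.69 | 0.220 | 86% | 68% | 0.154 | 99% | 92% |
| 0.02 | 2.38 | 0.261 | 73% | 55% | 0.183 | 95% | 82% |
| 0.05 | 4.45 | 0.357 | 47% | 35% | 0.250 | 76% | 58% |

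**Step 3: limits.** With a Center ICC of exactly 0, power on 6 df is 97.4% at SD 2.0 and 99.98% at SD 1.4. On 6 df it falls below 80% once the Center ICC exceeds about 0.014 (SD 2.0) or 0.044 (SD 1.4).

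**Step 4: is the loss only a small-sample effect?** No. The normal formula for eight Centers at SD 2.0, with no degrees-of-freedom penalty, still gives 95.4%, 86.6% and 61.2% at the three ICCs.

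**The case against.** **The loss depends on values the article does not give.** This stands. Every ICC above is an assumption. At SD 1.4 and a Center ICC of 0.01, power is still about 99% on 6 df. A reader might infer that the trial is underpowered; the article does not establish that.

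**The paired figures are a worst case.** This also stands. They charge the cost of pairing in degrees of freedom and credit none of its benefit, although the matching uses HbA1c and other covariates and the Discussion keeps pairs within a district. The Statistical analyses section does not specify a paired test.

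**The simulation may have been sounder than its description.** It does not say how many sites it used; only the check names 40. But the article keeps sites and Centers distinct, and the only cluster terms it lists are site and provider. As described, the simulation has no Center effect.

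**Two stronger readings are tempting but not supported.**
- A reader might say the 100.0% fails even without clustering, because n = 560 and SD 2.0 give 99.7%. That takes 2.0 as the residual SD. The article does not say whether it is a raw, change or residual SD, and the planned analysis of covariance adjusts for baseline. If 2.0 is a raw SD and the correlation with baseline is 0.5 (an assumption), the residual SD is 2.0 × √(1 − 0.25) = 1.73 and unclustered power is 99.98%, which prints as 100.0%.
- A reader might see a contradiction in the Setting criterion that "the site agrees to be randomized to either arm of the study". It is an eligibility condition: a site accepts whichever arm its Center draws. It is consistent with randomizing Centers.

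**Conclusion.** The concern holds as a mismatch between the unit randomized and the unit used for power. Eight Centers are allocated, while the power section counts 40 sites in its check and names no Center effect in its simulation. The 100.0% should not stand as the power of this design.

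The size is a range. On 6 df, for assumed Center ICCs from 0.01 to 0.05, power runs from about 86% down to 47% at SD 2.0, and from about 99% down to 76% at SD 1.4. These figures assume equal Centers of 70 analysed patients and a single level of clustering. Effective matching, or baseline adjustment beyond what the chosen SD already reflects, could recover some of the loss.

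The abstract's 20 sites against 40 in the Methods is a separate editorial discrepancy. It leaves the cluster count unclear but does not drive the power result.

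**What to change.** 1. Withdraw both 100.0% statements.
2. Add a Center random effect to the simulation, above site and provider, and state the variance components used.
3. Restate power for eight Centers, four per arm, about 70 analysed patients each, with small-sample degrees of freedom: 6, or 3 if the analysis keeps the pairs. Give a table over Center ICC 0.01 to 0.05 for SD 1.4 and SD 2.0.
4. Say whether 2.0 is a raw, change or residual SD.
5. Base the Center ICC on the trial's own baseline HbA1c, or on the 934-patient survey if it recorded Center. The pilot had 80 patients over eight Centers, about ten each, which is too few. Eight Centers also give an imprecise ICC, so keep the range in the table.
6. State one design throughout, namely eight randomized Centers, 40 sites and 800 patients, and correct the abstract's 20 sites.

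The cost is a re-run simulation, a reworded section and a less favourable stated power. No extra patients are needed.
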